### Sample size calculation

2.5

The sample size calculation for the present exploratory and feasibility evaluation within the ‘EMDR Pain Therapy Network’ is primarily based on the need to obtain meaningful data on the feasibility and efficiency of the network structures. Considering the aim of assessing the feasibility of a possible future randomised controlled trial, a minimum number of 20 therapists will be recruited, each of whom should enrol at least 10 patients in the trial. This results in a total of at least 200 patients.

This sample size is appropriate for the following reasons:

It enables a comprehensive assessment of the efficacy and side effect profiles of EMDR therapy for chronic pain.It is suitable for testing the feasibility of an accompanying evaluation in the outpatient setting, including documentation quality and patient satisfaction.

The results of the evaluation of the initial sample of 200 patients will be crucial in planning a larger multicentre trial. They should show whether the network is able to recruit enough patients and provide high quality data, and whether the therapeutic practices within the network are sufficiently standardised to conduct a randomised controlled trial.

It is important to note that this number of cases does not have to be the definitive end of the trial. Rather, once this initial target number has been reached, an interim analysis should be carried out to assess the logistical and administrative aspects of the study implementation, in addition to the scientific aspects. On this basis, an adapted or expanded recruitment strategy can be developed for the next phase of the study.

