### Statistical analyses overview

4.2

The primary aim of the ‘EMDR Pain Therapy Network’ is to generate a high-quality dataset that facilitates the investigation of future effectiveness measures, response rates, and potential predictors for both response and non-response. This dataset will provide broad opportunities for exploratory analyses to address future research questions. Within the network, specific questions and analyses are pre-planned:

Descriptive Analysis: To characterise the sample, descriptive statistics will be employed, covering demographic data, clinical characteristics, and outcome criteria. Continuous variables will be described using means, standard deviations, medians, and interquartile ranges. Categorical variables will be presented through frequencies and percentages.Effectiveness Outcome Analysis: The effectiveness of EMDR therapy will be evaluated by calculating effect sizes using Cohen’s d, with t-tests to determine these values. Response and non-response rates will be analysed using binary logistic regressions, with the PGIC and TGIC scales as dependent variables.Adverse effect Outcome Analysis: Adverse effects will be quantified through frequency analysis for each item of the NEQ questionnaire, and serious adverse events (SAEs) will be described using descriptive statistics, analysing their correlation with EMDR therapy.Therapist Influence: The impact of therapists on treatment outcomes will be explored using multivariate models or regression analyses, considering various contextual factors such as different therapy approaches, therapist experience.Analysis of predictors: Predictors for therapy success will be identified through multivariate regression analyses, using data from multidimensional phenotyping as independent variables.Feasibility and Practicability Assessment: The practicability of the evaluation process will be assessed by analysing dropout rates, missing values, and the variability of inclusion rates per therapist. An intention-to-treat analysis will be conducted, and satisfaction with the evaluation will be measured using z-scores.

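### Patients are nested in at least 20 therapists, but the named t-tests and logistic regressions make no stated allowance for it, so precision is overstated if the therapist ICC is above zero

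*Protocol article*

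**What the plan says.** Section 2.5 (Sample size calculation) sets the structure of the sample: "a minimum number of 20 therapists will be recruited, each of whom should enrol at least 10 patients in the trial". It adds: "This results in a total of at least 200 patients". The number is described as "primarily based on the need to obtain meaningful data on the feasibility and efficiency of the network structures"; no significance level, power, effect size or ICC is given.

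Section 4.2 (Statistical analyses overview) lists the pre-planned analyses. Effectiveness on continuous outcomes is expressed as Cohen's d, "with t-tests to determine these values". For response it says: "Response and non-response rates will be analysed using binary logistic regressions, with the PGIC and TGIC scales as dependent variables". Neither entry mentions therapist.

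Therapists appear as a separate item: "The impact of therapists on treatment outcomes will be explored using multivariate models or regression analyses". The covariates it names are the therapist's experience and the approach taken. The predictor analysis is a further item and uses regression on the patients' phenotyping data.

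**The concern.** A t-test and a binary logistic regression, as named, treat each patient as an independent observation. The design makes that doubtful. Under section 2.3 therapists choose which patients to treat and report. Section 2.2 gives them wide latitude in how they run sessions and documents that latitude instead of restricting it. Table 2 has the therapist complete the TGIC, so one rater scores every patient in the cluster on one of the two named response variables. Each of these makes outcomes more alike within a therapist than between therapists. The plan itself expects therapist effects, since it sets out to explore them.

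The therapist influence item does not settle the matter. It leaves the model class open, and nothing carries therapist into the effectiveness analyses. Therapist experience takes only about 20 independent values. An ordinary regression would test it as though there were 200.

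What is at stake is precision, not the direction of the results. Section 2.5 says the results on the first 200 patients will be crucial in planning a larger multicentre trial. Overstated precision would carry into that planning. The ICC that such a trial needs would also not be produced by the analyses as named.

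**Working it through.** **Inputs from the document.** Therapists: at least 20. Patients per therapist: at least 10. Total: at least 200 (all section 2.5). Methods: t-tests and binary logistic regressions (section 4.2).

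**Assumptions.** The document gives none of these: ICC 0.02, 0.05 or 0.10; two-sided 5% level; equal clusters at the planned minimum of m = 10.

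**The plan's own figure.** 20 × 10 = 200. It reproduces exactly, as a product with no power formula behind it.

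**Formulas.**
- Design effect: DE = 1 + (m − 1) × ICC = 1 + 9 × ICC
- Effective sample size: 200 / DE
- Correct interval width relative to the naive one: √DE
- Actual type I error of a naive 5% test of a mean: 2 × [1 − Φ(1.96 / √DE)]
- Half-width for d, in SD units of the change score: naive 1.96 / √200 = 0.139; correct 1.96 × √(DE / 200)
- Half-width for a 50% response rate: naive 1.96 × √(0.25 / 200) = 6.9 points; correct 1.96 × √(0.25 × DE / 200)

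| Assumed ICC | DE | Effective N | √DE | Type I error | Half-width, d | Half-width, 50% rate |
|---|---|---|---|---|---|---|
| 0 | 1.00 | 200 | 1.000 | 5.0% | 0.139 | 6.9 points |
| 0.02 | 1.18 | 169 | 1.086 | 7.1% | 0.151 | 7.5 points |
| 0.05 | 1.45 | 138 | 1.204 | 10.4% | 0.167 | 8.3 points |
| 0.10 | 1.90 | 105 | 1.378 | 15.5% | 0.191 | 9.6 points |

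For example, at ICC 0.05: DE = 1 + 9 × 0.05 = 1.45; 200 / 1.45 = 138; √1.45 = 1.204; 1.96 / 1.204 = 1.63, whose two-sided tail is 10.4%.

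**Simulation check, mean change.** One-sample t-test on change scores, 20 × 10, 10,000 runs per ICC. It rejected a true null in 4.9%, 6.8%, 10.5% and 15.3% of runs at ICC 0, 0.02, 0.05 and 0.10, in line with the formula.

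**Simulation check, logistic regression.** Ordinary logistic regression with one null therapist-level and one null patient-level predictor, 2,000 runs per ICC (ICC on the latent scale):
- Therapist-level predictor: 5.5%, 6.1%, 10.0% and 13.5% false positives at ICC 0, 0.02, 0.05 and 0.10.
- Patient-level predictor drawn independently of therapist: 4.0% to 5.2% throughout, so not inflated.

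**Unequal caseloads.** With coefficient of variation CV, DE = 1 + [(1 + CV²) × m − 1] × ICC. At an assumed CV of 0.6 and a mean of 10, DE is 1 + 12.6 × 0.05 = 1.63 (effective N 123) at ICC 0.05, and 1 + 12.6 × 0.10 = 2.26 (effective N 88) at ICC 0.10. A mean of 10 with any spread means that some therapists fall short of the planned 10, so this row describes a partly missed target. Section 4.2 does plan to examine how inclusion rates vary between therapists.

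**The case against.** The strongest reply is that this is an overview in a condensed article. Random-effect structure, variance estimator and degrees of freedom usually belong in the analysis plan. Naming binary logistic regression does not exclude a random intercept or cluster-robust errors, and the open wording of the therapist item could cover a multilevel model. That is fair as far as it goes, and it means the final analysis may yet be sound. It does not remove the point. The article goes beyond silence: it names a t-test, which takes no account of clustering, for a sample that it builds as clusters. It also confines therapist to a separate exploratory item.

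Three further objections stand and limit the claim:

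- A reader might infer that therapist-level predictors will be falsely significant. The document does not support that. It gives no ICC. The simulations show a raised error rate that depends on the assumed ICC: about 6% at 0.02 and none beyond chance at zero.
- A reader might extend the fault to all predictor analyses. The phenotyping variables are patient-level, and a patient-level predictor that does not vary by therapist showed no inflation. Only predictors that differ systematically between therapists' caseloads would be affected.
- The plan mentions no confidence intervals and gives the t-test a limited role. The point estimate of d is little affected. The fault lies in any interval or p-value derived from these tests.

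The study is also a feasibility evaluation. Recruitment capacity and documentation quality, which section 2.5 wants to learn about, do not depend on the standard error of d.

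**Conclusion.** The point holds in this form: as named, the effectiveness and response analyses make no allowance for therapist clustering, and the therapist-level analysis does not commit to one. With a positive ICC, standard errors are too small for mean change, response rates and therapist-level covariates such as experience and approach.

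The size depends wholly on an ICC that the document does not supply. It is modest at 0.02 and material at 0.05 to 0.10. The figures rest on equal clusters at the planned minimum of 20 × 10. Both numbers are minima, so the achieved sample may be larger, but larger caseloads per therapist also raise the design effect.

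Severity is moderate. The work is exploratory and no power claim fails, because 200 was not derived from one. Treating the point as one that invalidates the study would go beyond the document.

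**What to change.** In section 4.2:

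- Analyse mean change, PGIC/TGIC response and therapist-level effects with linear and logistic models that include a random intercept for therapist. GEE or cluster-robust standard errors would serve equally well.
- State a small-sample correction suited to about 20 clusters, for example Satterthwaite or Kenward–Roger degrees of freedom for the linear model, or a bias-corrected sandwich variance with a t reference.
- Test therapist experience and therapy approach at the therapist level. With 20 therapists and one such covariate, that leaves about 20 − 2 = 18 degrees of freedom.
- Report the ICC for each main outcome with its confidence interval, for use in planning the randomised trial.

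The cost is wider intervals, a few lines of text and slightly more analysis work. No new data collection seems necessary: the plan already intends to report inclusion rates per therapist, which implies that each patient can be linked to a therapist, although the article does not say so outright.

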Fear of Pain Questionnaire (FPQ)	Measure to assess fear of different stimuli usually causing pain (30 items) (McNeil and Rainwater, 1998)	X	X	
Widespread Pain Index (WPI)	Assessment of the spatial extent of pain (distinguishing between 19 body areas and 5 body regions) (Galvez-Sánchez et al., 2020)	X	X	
Multidimensional Pain Inventory (MPI-D)	12-scale inventory to assess important dimensions of chronic pain experience (52 items) (Kerns et al., 1985)	X	X	X
Chronic Pain Grade Scale (CPG)	7-item measure designed to evaluate pain intensity and pain-related disability in adults with chronic pain conditions (7 items) (Dixon et al., 2007)	X	X	
Pain-Related Self Statement Scale (PRSS)	Measure to assess situation-specific aspects of patients’ cognitive coping with pain (18 items) (Flor et al., 1993)	X	X	
Western Ontario and McMaster Universities Arthritis Index (WOMAC)	Assessment of pain, stiffness and functional impairment (24 items) (Bellamy, 2005)	X	X	
Trier Inventory of Chronic Pain (TICS)	The questionnaire measures six aspects of chronic stress (57 items) (Schulz et al., 2004)	X		
Brief Symptom Inventory (BSI)	Questionnaire to record subjective impairment due to physical and psychological symptoms (53 items) (Geisheim et al., 2002)	X		
Pain Sensation Scale (Schmerzempfindungsskala, SES)	24-item questionnaire to measure and differentiate description of subjectively perceived pain (Geissner, 1995)	X	X	
Past stress experiences and post-traumatic distress				
Critical life events and life crises (Kritische Lebensereignisse und Lebenskrisen, KLL)	32-item inventory to assess critical life events and life crises (Tennant and Andrews, 1976)	X		
Posttraumatic Diagnostic Scale (PDS)	Measure to assess PTSD symptom severity in the last month (24-items) (Foa et al., 1997)	X		
Somatic illnesses and high psychological stress				
Oswestry-Disability Inventory (ODI)	Questionnaire to assess pain-related functional restrictions in patients with back pain (10 items) (Fairbank and Pynsent, 2000)	X	X	X
Compliance Questionnaire for Rheumatology (CQR5)	5-item questionnaire measuring compliance with rheumatic disease treatment (Hughes et al., 2013)	X	X	
Study-specific evaluation form				
Negative Effects Questionnaire (NEQ)	Questionnaire to assess unwanted and negative effects of the treatment (32 items) (Rozental et al., 2016)		X	

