Inventory for Assessing Negative Effects of Psychotherapy (INEP)	Questionnaire to assess unwanted and negative effects of the treatment (21 Items) (Ladwig et al., 2014)		X	
Patient’s global impression of change (PGIC)	Patient’s global impression of change (1-items) (Hurst and Bolton, 2004)		X	X
Additional Patient-Reported Outcome Measures (PROMs)	Assessment of Change in medication after treatment (1-item) (Weldring and Smith, 2013)		X	X
Agnew Relationship Measure Patient (ARM-5)	5-item questionnaire about client-therapist alliance (Cahill et al., 2012)		X	

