Severe adverse events (SAE)	Assessment of severe adverse events and their relationship to therapy (6 items)	For each session
Therapist questionnaire	6-item questionnaire about therapists’ experience with EMDR	T_0_
Therapists’ global impression of change (TGIC)	2-item questionnaire about therapists’ global impression of change of their patients (Ferguson and Scheman, 2009)	T_1_
Agnew relationship measure therapist (ARM-5)	Questionnaire about client-therapist alliance (5 items) (Cahill et al., 2012)	T_1_

The proposed case conceptualisation in the treatment of chronic pain follows a three-stage approach according to the standard model of past, present and future, distinguishing between pain-related and non-pain-related trauma.

The classic protocol provides for a systematised target selection, in which, in cases in where the pain is associated with traumatic and (even today!) stressful experiences, desensitisation and reprocessing of these experiences should be started first (Borst et al., 2024; Tesarz et al., 2015). In cases where either no traumatic experience can be identified as the trigger or where the traumatic event has been reprocessed more successfully in the meantime, the distressing memories and thoughts associated with the pain should be processed. After processing distressing memories and thoughts, and in cases where no distressing memories or thoughts can be identified initially, the pain can also be focussed on directly using the specific pain protocol. In cases where patients gain access to new, previously repressed experiences during pain processing, reactivated memories can be revisited and further processed during the course of therapy using the standard protocol or a modified standard protocol. Finally, or in addition, it is possible to use the standard protocol, modified standard protocol, the absorption exercise or the flash-forward protocol to alleviate dysfunctional fears of illness, future pain crises and potential pain triggers.

In practice, however, it has been shown that other targets are relevant in the treatment of patients with pain in addition to classic traumas and the pain itself.

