### Procedure

2.3

Outpatient therapists will identify patients with chronic pain conditions for whom they would like to provide an EMDR intervention as part of their regular psychotherapy. In a first step, these patients will be informed by the therapists and will give their written consent to be contacted by the study team at the University Hospital of Heidelberg. There will be no specific recruitment; rather, therapists will decide which patients to admit for outpatient therapy and which to report to the EMDR network. Within a further diagnostic appointment, the Structured Clinical Interview for the Diagnostic and Statistical Manual for Mental Disorders (SCID-5) (First et al., 2015) will be conducted by trained research assistants via telephone. Figure 1 illustrates the subsequent steps of data acquisition, which will be conducted online using the web application REDCap (Harris et al., 2019). First, eligible patients undergo a comprehensive baseline assessment (T_0_), including a broad range of self-rating instruments on various domains of relevant symptomatology, physical and emotional functioning, and other potential mechanistic and predictive factors. When patients and therapists decide to end the therapy, we will conduct a post-treatment outcome assessment (T_1_) including main outcomes, relevant measures from the baseline assessment, therapeutic alliance, therapy evaluation, and potential adverse effects associated with the treatment. Finally, three follow-up assessments (T_2_–T_4_) will be implemented 4 weeks and 3 months and 12 months post-treatment.

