#### Adverse effects associated to EMDR therapy and safety outcomes

4.1.5

1. Negative Effects: These are intended to be captured using the Negative Effects Questionnaire (NEQ) and the Inventory for Assessing Negative Effects of Psychotherapy (INEP).

2. Severe Adverse Events (SAEs): These will be documented and examined for potential causal relationships with EMDR therapy.

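### Dedicated harm capture ends with therapy although follow-up runs to 12 months, and the stated harm analysis leaves out INEP and asks for an SAE correlation that has no comparator

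*Protocol article*

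**What the plan says.** The protocol article gives harms a prominent place. The abstract calls the side effects of EMDR in chronic pain poorly understood. Objectives (1.1) list longitudinal research on individual treatment effects, adverse ones included. Sample size calculation (2.5) claims that 200 patients allow a comprehensive view of the side-effect profile.

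Section 4.1.5 names two negative-effects measures: "These are intended to be captured using the Negative Effects Questionnaire (NEQ) and the Inventory for Assessing Negative Effects of Psychotherapy (INEP"). It adds that SAEs will be documented and examined for a causal link with EMDR.

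The schedule is as follows:
- Table 1 (Material, 2.1) gives NEQ (32 items) and INEP (21 items) one mark each, in the T1 column. This agrees with Procedure (2.3), which places "potential adverse effects associated with the treatment" in the post-treatment assessment.
- Table 2 (2.2) gives therapists an SAE form, described as "Assessment of severe adverse events and their relationship to therapy (6 items"), for completion at each session. Section 2.3 places this documentation in the treatment period and gives hospital admission and suicidality as examples.
- Section 2.3 sets T2, T3 and T4 at 4 weeks, 3 months and 12 months after treatment.

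The harm analysis in 4.2 reads "Adverse effects will be quantified through frequency analysis for each item of the NEQ questionnaire". SAEs are to be summarised descriptively, "analysing their correlation with EMDR therapy".

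**The concern.** The study contacts patients three times in the year after therapy but schedules no instrument then that asks about adverse events. A delayed harm could therefore appear only as a worse score, with no record of what happened or whether it was thought related to treatment. Unlike a gap in the analysis wording, this cannot be repaired once the data are in. The results are meant to inform a randomised trial, so that trial's safety planning would rest on events reported during therapy or at its end.

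Two statements in 4.2 make this worse. One of the two named negative-effects measures has no analysis in the adverse-effects item. And the SAE sentence asks for a quantity that the design does not supply if it is read as receiving versus not receiving EMDR.

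**Working it through.** No power or precision figure is at issue. The stated sample reproduces: 20 therapists × 10 patients = 200. The rest is a comparison of sections.

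**Step 1: harm tools by time point (Tables 1 and 2; 2.3)**

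| Tool | During therapy | T1 | T2–T4 |
|---|---|---|---|
| SAE form (therapist) | each session | – | – |
| NEQ | – | yes | – |
| INEP | – | yes | – |
| PGIC, medication change | – | yes | yes |
| HADS, SF-12, MPI-D, ODI (also at T0) | – | yes | yes |

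Dedicated harm tools in use up to and including T1: 3 of 3. At T2–T4: 0 of 3. With 200 patients and full attendance, 200 × 3 = 600 planned follow-up assessments would pass without an SAE question. Section 4.1.6 says Table 1 covers all measures at the data-collection points, so the blank cells can be read as the intended schedule.

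**Step 2: what the continuing measures can show**

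PGIC runs from very much improved to very much worse, so worsening is visible at each follow-up. A change in medication, or a fall in function or mood scores, is visible too. None of these identifies an event such as a hospital admission, or records an attribution to treatment.

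**Step 3: outcomes set against analyses**

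Negative-effects questionnaires named in 4.1.5: 2. Named in the adverse-effects item of 4.2: 1. In items, 32 + 21 = 53 are collected, and 32 have an analysis named there. Each patient completes NEQ once, so its item frequencies are already proportions of patients. What is not named is a summary across items, such as the proportion with at least one negative effect attributed to treatment.

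**Step 4: the SAE correlation**

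Let X = 1 if a patient receives EMDR and Y = 1 if the patient has an SAE. The correlation is cov(X, Y) / (SD(X) × SD(Y)). The inclusion criteria require that EMDR is planned for every patient, and no comparison group is described. If X = 1 for all, then SD(X) = 0 and cov(X, Y) = 0, and the ratio is 0/0, which is undefined. Patients who leave before any EMDR would give X some variation, but they would be a self-selected group and not a designed control. What one arm can supply is the therapist's relationship rating, which Table 2 already collects and which the causality wording in 4.1.5 points to.

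**Step 5: terms**

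Sections 2.2, 2.3 and 4.1.5 speak of *severe* events; 4.2 expands the same abbreviation as *serious*. Severity grades intensity, while seriousness refers to consequences such as hospital admission, so the two can select different events.

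**The case against.** The strongest reply has four parts.

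- **Follow-up is not blind to harm.** A reader might infer from the empty NEQ, INEP and SAE cells that nothing on harm is collected at T2–T4. Table 1 does not support that: six measures continue and can show deterioration. This part stands, and it limits the point to dedicated, event-level and attributed harms.
- **The correlation is probably loose wording.** Taken with 4.1.5 and the form in Table 2, the sentence most plausibly means a case-by-case relatedness assessment, which a single arm can provide. Associations with session content or technique, which vary and are documented, are also possible. This stands as to intent. The sentence still names the wrong quantity and should be changed.
- **Section 4.2 is an overview in an article.** Its descriptive item covers outcome criteria in general and could take in INEP, and a fuller plan may exist. So a reader should not conclude that INEP has been dropped or will go unanalysed, only that the adverse-effects item names NEQ and not INEP. Alone, that gap would be a clarification.
- **Light follow-up is a design choice.** The evaluation is meant to disturb routine care as little as possible. That is a fair reason for not repeating 53 items three times. It does not explain the absence of even a short SAE question, given the stated aim of longitudinal research that includes adverse effects.

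**Conclusion.** The concern holds in limited form. The main defect is in data collection: 0 of 3 dedicated harm tools are in use over 12 months of follow-up, so SAEs after the last session are not recorded and the promised side-effect profile will lack delayed events. The missing INEP analysis, the correlation wording and the two SAE terms are secondary and are settled by editing.

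This rests on reading the single NEQ and INEP marks in Table 1 as T1, which the table layout and section 2.3 both support, and on the SAE form being used only at sessions, as Table 2 and section 2.3 state.

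A reader might want to express the gap as a share of total observation time. The documents do not allow it: therapy ends when patient and therapist decide, and no duration is given. Nor does the sample of 200 measure what is lost, because an upper limit on a rare event rate computed from the number of patients does not depend on how long each was asked about events. The protocol also gives no reason to expect a particular rate of late harms, so the size of the resulting bias is unknown. The change is worth making because it is cheap and the data cannot be recovered later.

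**What to change.** 1. Add a short SAE self-report, adapted from the 6-item therapist form, to the existing online assessments at T2, T3 and T4.
2. In 4.2, analyse INEP alongside NEQ. For each, report item frequencies and the proportion of patients with at least one negative effect attributed to treatment, with confidence intervals that allow for clustering by therapist.
3. Replace the correlation wording with SAE incidence and exact confidence intervals, plus a table of the relationship-to-therapy rating already collected. Show events during therapy and during follow-up separately, since the informant differs.
4. Report the worsening categories of PGIC at T1–T4 as a deterioration outcome.
5. Reconcile *severe* and *serious* across 2.2, 2.3, 4.1.5 and 4.2, and define the term once.

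Items 2 to 5 need only changes of wording and analysis, using data already scheduled. Item 1 costs slightly more patient time at three existing contacts. The therapist form also has to be reworded for patients, and the study team needs a process for handling reports that arrive online.
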